|                                                                         | 
Primary analysis
 
Those included: Infants who are residents in a Matlab village on the date upon which they turn 6 weeks (42 days) of age between Apr 1, 2009 (for ICDDR,B service area villages) or Nov 1, 2008 (for government service area villages) and March 31, 2011. In-migrant infants will be included if they in-migrate to a Matlab village when they are between 6 weeks and 20 weeks of age between Apr 1, 2009 (ICDDR,B service area) or Nov 1, 2008 (Govt service area) and Mar 31, 2011.
 
Follow-up period: Person-time will be counted from 6 weeks of age or age of in-migration until two years (731 days) of age or March 31, 2011, whichever comes first.
 
Secondary analysis
 
Those included: Identical to those in the “overall effectiveness-primary analysis” population plus those infants residing in study area villages who are between 6 and 20 weeks of age on Apr 1, 2009 (ICDDR,B service area) or on Nov 1, 2008 (Govt service area). Inclusion will then be restricted to those who received OPV1 (exclusive of birth dose) in a Matlab village after Apr 1, 2009 (ICDDR,B service area) or Nov 1, 2008 (Govt service area).
 
Follow-up period: Person-time will be counted from the date of OPV1 (exclusive of birthdose) until two years (731 days) of age or March 31, 2011, whichever comes first.
 |

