|                                             | 
Three groups are definable for analysis of indirect effects.
 
Indirect Population 1
 
Those included: Infant and child residents of Matlab who are at least 20 weeks of age as of Apr 1, 2009 (ICDDR,B service area villages) or Nov 1, 2008 (Govt service area villages) or in-migrants to the study area who are between 20 weeks and 2 years of age during the study period. Treatment group assignment for these children will be determined by village of residency at the time that first allows them to be included in this population.
 
Follow-up period: Person-time will be counted from Apr 1, 2009 (ICDDR,B service area villages) or Nov 1, 2008 (Govt service area villages) or date of in-migration until two years of age (731 days) of age or March 31, 2011, whichever comes first.
 
Indirect Population 2
 
Those included: Infants who resided in Matlab between 6 and 20 weeks of age after Apr 1, 2009 (ICDDR,B service area) or after Nov 1, 2008 (Govt service area).
 
Follow-up period: Person-time will be counted from Apr 1, 2009 (ICDDR,B service area villages) or Nov 1, 2008 (Govt service area villages) or date of in-migration until receipt of OPV1, the child turns two years of age (731 days), or March 31, 2011, whichever comes first.
 
Indirect Population 3
 
Those included: All infants or children resident of the study area aged between 6 weeks and 2 years at some point during the study period.
 
Follow-up period: All person-time contributed during the study period. The analysis will account for receipt of vaccine (this will include any
 |

|  |                                                                                                |
|--|------------------------------------------------------------------------------------------------|
|  | indirect effects that also accrue to those who receive Rotarix, which is not 100% protective). |
|--|------------------------------------------------------------------------------------------------|

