### 3.3 Baseline Characteristics

Summaries will be provided to describe the subject populations in this study by study arm. Only subjects with data will be included in the summaries, i.e. missing data will be counted as missing.

We will report baseline characteristics in two ways:

- 1) Data on infants and children who are aged 6 weeks to 2 years residing in the service areas on November 1, 2008 (April 1, 2009)
- 2) Data on infants who are part of the Overall cohort of those who turn 6 weeks of age over the course of the entire study period, or who in-migrated at an age less than 24 weeks

Also by age groups: 6 weeks to 1 year, 1 to 2 years. Also by sex. Also, the proportions of children aged 12-23 months within each randomization unit with 1, 2, and 3 OPV doses. Also, by SES quintile...

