### *Primary Aim*

*To evaluate the population (overall) (Halloran, et al., 1997) effectiveness of Rotarix in reducing rates of acute diarrhoea due to rotavirus, as detected by patients admitted to a study treatment facility, among all infants and young children from villages where Rotarix is introduced compared to among those from villages where Rotarix is not introduced.*

Main analysis, on Overall population: first episodes of rotavirus diarrhea. A Poisson regression with Pearson scale parameter (calculated at the village level) will be fit, offset with person-years of exposure, with a dummy covariate for village randomization arm status and a dummy covariate for villages in the Matlab service area (corresponding to the stratified randomization).

Note that this overall effectiveness is a function of vaccine efficacy and vaccine coverage. Since over 90% coverage is expected, this will not be much different from a total effects analysis. Also, if there are any indirect effects that act to reduce transmission, these may exert a differential effect over time, as it is not until near the end of the study period that the entire population of children under 2 years of age will be saturated with vaccine.

Additional analysis: same as main analysis, but including **all** episodes of rotavirus diarrhea, not just first episodes. The scale parameter at the randomization unit level also accounts for all within-child correlation, so the same analysis approach can be used.

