### *Secondary Aims*

*1. To evaluate the total effectiveness of Rotarix in reducing rates of acute diarrhoea due to rotavirus, as detected by patients admitted to a study treatment facility, among vaccinated infants and young children from villages where Rotarix is introduced compared to unvaccinated infants and young children from villages where Rotarix is not introduced.*

Main analysis, “overall effectiveness” primary analysis population: with the modification of starting observation time at 12 weeks instead of 6 weeks of age. A Poisson regression with Pearson scale parameter (calculated at the village level) will be fit, offset with person-years of exposure, with a dummy covariate for village randomization arm status and a dummy covariate for villages in the Matlab service area.

Additional analyses:

- a. As in 1., but for all (not just first) cases of rotavirus diarrhea.
- b. As in 1. and 1.a, but for the mITT population.

*2. To evaluate the indirect effectiveness of Rotarix in reducing rates of acute diarrhoea due to rotavirus, as detected by patients admitted to a study treatment facility, among unvaccinated*

*infants and young children from villages where Rotarix is introduced compared to those from villages where Rotarix is not introduced.*

*Analyses are given according to the populations a, b, c given above.*

a) Those aged at least 20 weeks as of Nov 1, 2008 (Apr 1, 2009), with censoring at earliest of 2 years of age or Mar 31, 2001, whichever comes first. Also included are those who in-migrate between ages 20 weeks-2 years. Poisson regression as described above will be used; all cases (first and subsequent) will be used.

b) Those in the Overall population, but with censoring at first OPV dose. Because of the high coverage, this will not comprise many person-years. Poisson regression as described above will be used; all cases (first and subsequent) will be used.

c) All person-time contributed by infants or children who were between 6 weeks and 2 years of age at some point during the study period.

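### Indirect Population 1 has two different in-migrant rules, and neither keeps out children who lived in the study area at vaccination age, so Rotarix recipients can be analysed as unvaccinated

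*SAP*

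**What the plan says.** Secondary Aim 2 (section 3.5) concerns unvaccinated children in Rotarix villages compared with children in villages without Rotarix. Indirect Population 1 is one of three populations for it.

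- **Section 3.2, Indirect Population 1.** Besides children already 20 weeks or older at launch, it admits "in-migrants to the study area who are between 20 weeks and 2 years of age during the study period". Person-time runs from the area start date "or date of in-migration until two years of age (731 days) of age or March 31, 2011, whichever comes first". Arm is set by "village of residency at the time that first allows them to be included in this population".
- **Section 3.5, Secondary Aim 2(a).** The same population is restated with a different clause: "Also included are those who in-migrate between ages 20 weeks-2 years". The analysis is the Poisson regression of the primary aim, with terms for arm and service area, counting all episodes.
- **Section 3.2, overall effectiveness, primary analysis.** "In-migrant infants will be included if they in-migrate to a Matlab village when they are between 6 weeks and 20 weeks of age". These infants are therefore in the vaccine-eligible cohort.
- **Section 3.2, Indirect Populations 2 and 3.** Population 2 stops person-time at OPV1, and Population 3 takes receipt of vaccine into account. Population 1 has neither provision.
- **Section 3.5, opening text.** For all analyses, a child keeps the village in which he or she first entered the Overall population.
- **Section 3.3.** For the baseline tables, the Overall cohort includes infants "who in-migrated at an age less than 24 weeks".

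**The concern.** Population 1 is meant to hold children who were too old to be offered Rotarix in the study, so that any difference between arms reflects reduced transmission. That works only if children who could have been vaccinated are kept out. In section 3.2 the age limit attaches to the study period and not to arrival. An infant who moves in at 8 weeks and is offered Rotarix satisfies it on passing 20 weeks.

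The Aim 2(a) wording closes that route but leaves another open. A child vaccinated in a Rotarix village who moves away and comes back at, say, 10 months is an in-migrant of eligible age.

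Rotarix recipients can occur in Rotarix villages and not, by design, among children who stayed in control villages. Those counted in the Rotarix arm lower its rate by direct protection, and the fitted rate ratio would show this as an indirect effect. The error would favour a positive finding on a secondary aim.

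**Working it through.** The SAP states no figure for this point, so there is none to reproduce. The check compares the definitions and then gives an illustration on stated assumptions.

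**1. Who can enter Population 1 through the in-migrant clause**

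| Child | Section 3.2, read literally | Aim 2(a) |
|---|---|---|
| Arrives at 6-20 weeks, stays past 20 weeks | Enters; also in the Overall population | Does not enter |
| Resident at 6-20 weeks, leaves, returns after 20 weeks | Can enter | Can enter |
| First arrives at 20 weeks to 2 years | Enters | Enters |

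Only the third row is the intended group. Neither definition asks about earlier residence or vaccination, and the model does not adjust for either.

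**2. Size on the literal section 3.2 reading**

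With no true indirect effect and equal underlying rates,

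apparent indirect effectiveness = m × s × c × VE.

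- m is the in-migrant share of Population 1 person-time. The SAP does not give it; the range assumed is 10-40%.
- s is the share of in-migrant person-time from children who arrived before 20 weeks. It is not given either. It is calculated by assuming arrivals uniform over age 0 to 731 days and over calendar time, with follow-up to the earlier of 731 days of age and March 31, 2011.
- c = 0.90, from section 3.5, Primary Aim: "Since over 90% coverage is expected".
- VE = 0.50. This is the overall effectiveness assumed in section 2.5, used here as a stand-in for direct protection.

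| | s | s × 0.90 × 0.50 | m = 10% | m = 40% |
|---|---|---|---|---|
| Arrivals before 20 weeks, government area | 29.8% | 13.4% | 1.3% | 5.4% |
| Arrivals before 20 weeks, ICDDR,B area | 28.3% | 12.8% | 1.3% | 5.1% |
| Arrivals at 6-20 weeks only, government area | 20.6% | 9.3% | 0.9% | 3.7% |
| Arrivals at 6-20 weeks only, ICDDR,B area | 19.7% | 8.9% | 0.9% | 3.6% |

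The result is about 1-5%. Varying VE from 30% to 70% widens it to between 0.197 × 0.90 × 0.30 × 0.10 = 0.5% and 0.298 × 0.90 × 0.70 × 0.40 = 7.5%.

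Two simplifications make these figures generous. Protection is counted from arrival, and 90% coverage is applied even to infants who arrive near 20 weeks with little of the vaccination window left.

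**3. Size on the Aim 2(a) reading**

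Only returning children remain. If f is the share of Rotarix-arm person-time that comes from Rotarix recipients, apparent indirect effectiveness = f × VE. At VE = 50%, f = 1% gives 0.5%, 5% gives 2.5% and 10% gives 5%. The SAP gives no return-migration rate, so f is unknown; the low end is more likely.

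**4. After the intended exclusion**

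With f = 0 the spurious effect from this source is 0.

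**The case against.** The strongest reply is that Aim 2(a) is the operative analysis text and does tie the limit to age at arrival. Section 3.2 can be read the same way: starting person-time at in-migration makes sense only if the child already qualifies on that day, and the 6-20-week arrivals are placed in the Overall population. This is a good argument about intent. It does not remove the conflict, because someone programming from section 3.2 could build the wider group. A reader might infer that the SAP has no age-at-arrival rule at all; Aim 2(a) shows otherwise.

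For returning children, it can be said that the section 3.5 migration rule keeps them in their first village. That rule assigns a village; it does not exclude anyone from Population 1, and it conflicts with Population 1's own assignment rule. The conflict also affects direction: under Population 1's rule, a vaccinated child who returns to a control village would pull the estimate the other way.

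Two further inferences are not supported:

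- **Membership in two analysis populations.** The 24-week limit in section 3.3 might suggest that arrivals at 20-24 weeks are both vaccine-eligible and not. That limit governs baseline tables only; analysis membership follows the 20-week limit in section 3.2.
- **A larger late-study bias.** The youngest launch residents, 140 days old at the start, reach 731 days after 591 days: June 15, 2010 in the government area and November 13, 2010 in the ICDDR,B area. From then on Population 1 is in-migrants only, so a reader might apply the 9-13% in-migrant figure to that period. Those shares were calculated over the whole study, and Aim 2(a) plans one pooled rate ratio, so no planned result corresponds to it.

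It also stands that this is one of three populations for one secondary aim, that Populations 2 and 3 deal with vaccination, and that the primary analysis is untouched.

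**Conclusion.** The concern holds in limited form. The SAP gives Population 1 two in-migrant rules, and under both of them Rotarix recipients can be counted in a group meant to be unvaccinated, with no censoring or adjustment to correct for it. When they are counted in the Rotarix arm, the bias is toward a false indirect effect.

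Its size cannot be established from the SAP. The illustration of about 1-5% belongs only to the literal section 3.2 reading and depends on the assumed migration pattern and in-migrant share. On the Aim 2(a) reading the effect is probably smaller. The change is still worth making, because the repair is cheap and the error would favour a positive claim. The 24-week limit in section 3.3 is an editorial mismatch and contributes nothing to the bias.

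**What to change.** Use one in-migrant clause in section 3.2 (Indirect Population 1) and in Secondary Aim 2(a): children who in-migrate at 20 weeks to under 2 years of age, on or after the actual first date of Rotarix administration in the area, and who were not resident in any study village between 6 and 20 weeks of age after that date.

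- Apply it identically in both arms from HDSS residence history. Excluding or censoring on Rotarix receipt would remove children from one arm only.
- Use the actual first date. Section 2.1 says government-area vaccination began in September 2008, before the November 1, 2008 shorthand date. The same date difference should be checked for children resident at launch: one aged 20 weeks on November 1 was about 11 weeks old on September 1 (20 − 61/7 = 11.3).
- State that Population 1's village-assignment rule takes precedence over the general rule in section 3.5 for this population.
- Separately, change the 24-week limit in section 3.3 to the 20-week limit of section 3.2.

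The cost is SAP wording, one residence filter on existing data, and a small loss of in-migrant person-time.

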|                                                                 | 
MITT analysis
 
Those included: Infants in the “overall effectiveness-primary analysis” population from Rotarix villages plus those infants residing in Rotarix study villages who are between 6 and 20 weeks of age on Apr 1, 2009 (ICDDR,B service area) or on Nov 1, 2008 (Govt service area), regardless of receipt of Rotarix.
 
Follow-up period: Person-time will be counted from six weeks of age until two years (731 days) of age or March 31, 2011, whichever comes
                                                                                                                                                                                                                                                                                                                                                                                        |

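### Two secondary-aim follow-up rules in SAP 3.2 start the clock too early: Indirect Population 2 before birth, Direct MITT before launch or arrival

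*SAP*

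**What the plan says.** **Indirect Population 2 (SAP 3.2).** Members are "Infants who resided in Matlab between 6 and 20 weeks of age after Apr 1, 2009 (ICDDR,B service area"), with the parallel November 1, 2008 date for the government area. Person-time starts at the area launch date, "Nov 1, 2008 (Govt service area villages) or date of in-migration until receipt of OPV1, the child turns two years of age", or March 31, 2011. Neither birth nor 6 weeks of age is mentioned. Indirect Population 1 has the same start wording, but its residents are already at least 20 weeks old at launch, so there it fits.

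**Same analysis in SAP 3.5, Aim 2b.** "Those in the Overall population, but with censoring at first OPV dose. Because of the high coverage, this will not comprise many person-years". For the primary Overall population SAP 3.2 has "Person-time will be counted from 6 weeks of age or age of in-migration until two years (731 days) of age". The secondary Overall population starts at OPV1.

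**Direct MITT (SAP 3.2).** It takes the primary Overall "population from Rotarix villages plus those infants residing in Rotarix study villages who are between 6 and 20 weeks of age" on the launch date. The clock: "Person-time will be counted from six weeks of age until two years (731 days) of age or March 31, 2011". The primary Overall population admits late arrivals ("In-migrant infants will be included if they in-migrate to a Matlab village when they are between 6 weeks and 20 weeks of age"), so Direct MITT contains them too, but its follow-up rule leaves out the in-migration start.

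**Use.** Aim 2b is a Poisson regression offset by person-years. The Direct population enters a Cox model with first Rotarix dose as a time-varying covariate (3.5, Aim 3).

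**The concern.** The two rules fail in different ways.

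- **Indirect Population 2** counts time before birth. A resident child born in January 2010 would accrue 9 months (ICDDR,B area) or 14 months (government area) before being born. The genuine at-risk time, from 6 weeks to OPV1, is short, so the spurious time dominates the Poisson offset. The rate then approaches cases per infant, and a difference between arms in OPV1 timing or uptake can appear as an indirect effect.
- **Direct MITT** counts time before the SAP's launch date for infants aged 6-20 weeks on that date, and time before arrival for in-migrants. This falls essentially on the unvaccinated side. If no cases are captured in it, the unvaccinated rate is diluted and effectiveness is understated. If cases are captured, the comparator includes non-concurrent time.

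**Working it through.** The SAP gives no person-time figure for either population, so there is none to reproduce.

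**Inputs from the SAP.** Launch November 1, 2008 (government) and April 1, 2009 (ICDDR,B); end March 31, 2011; hence windows W of 880 and 729 days. Follow-up ends at 731 days of age, so at most 731 − 42 = 689 days from 6 weeks. Coverage is expected to exceed 90%.

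**Assumptions not in the SAP.** 6-week dates uniform over the window; the OPV1 delays, dose delays, coverage range and non-uptake values given below.

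**1. Indirect Population 2: pre-birth time**
- Born after launch: (880 − 42)/881 = 95.1% (government); (729 − 42)/730 = 94.1% (ICDDR,B).
- Mean pre-birth days: (838 × 839/2)/881 = 399; (687 × 688/2)/730 = 324. Maxima 838 and 687.

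**2. Indirect Population 2: denominator**
- If every infant receives OPV1 14 days after 6 weeks, the mean intended time is about 13.9 days. The literal rule adds W/2: 440 + 13.9 = 454 and 364.5 + 13.9 = 378 days, an inflation of about 33-fold and 27-fold. For delays of 56 down to 3 days the range is 8 to 148-fold.
- If 10% never receive OPV1: their mean follow-up is [(W − 689) × 689 + 689²/2]/W = 419 and 363 days, on average about 56 weeks. Intended time with an OPV1 lag of 2-4 weeks is 0.9 × 2 + 0.1 × 56 = 7.4 to 0.9 × 4 + 0.1 × 56 = 9.2 weeks. The added time is 63 and 52 weeks, mean 57.5. Inflation: 64.9/7.4 = 8.8 to 66.7/9.2 = 7.3.

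**3. Indirect Population 2: between-arm ratio**
- Balanced arms (true ratio 0.70, OPV1 at 14 days in both, event rate set high for stability): the simulated mean ratio is 0.70 under both rules. The 95% range of the relative denominator change is 0.98-1.02.
- Uptake differs (illustration: 10% non-uptake in control, 6% in Rotarix villages; true ratio 1.0). Rotarix time is 0.94 × 2 + 0.06 × 56 = 5.24 or 0.94 × 4 + 0.06 × 56 = 7.12 weeks. Apparent ratio: (5.24/62.74)/(7.4/64.9) = 0.73; (7.12/64.62)/(9.2/66.7) = 0.80.
- Timing differs (14 versus 21 days, government window): the ratio is multiplied by about (14/21)/(454/461) = 0.68, or 1.47 if reversed.

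**4. Direct MITT: pre-launch time**
- Infants 1 to 98 days past 6 weeks at launch: mean 49.5 pre-launch days, 98 × 49.5 = 4,851 days on a one-birth-per-day scale. They are 98/979 = 10.0% and 98/828 = 11.8% of infants.
- Post-launch time: about 368,960 + 98 × 639.5 = 431,631 (government); 264,921 + 62,671 = 327,592 (ICDDR,B). Pre-launch share of all time: 4,851/436,482 = 1.1%; 4,851/332,443 = 1.5%.
- Unvaccinated time at 90% coverage, first dose after 14 days: about 0.1 × 431,631 + 0.9 × 14 × 979 = 55,499; 0.1 × 327,592 + 0.9 × 14 × 828 = 43,192. Pre-launch share: 4,851/60,350 = 8.0%; 4,851/48,043 = 10.1%. Delays of 7 to 28 days give 7-11%; coverage of 80-95% widens this to 4-18%.
- True effectiveness 50%, no cases counted pre-launch: 1 − 0.5/(1 − 0.080) = 45.6%; 1 − 0.5/(1 − 0.101) = 44.4%. Range 44-46% at 90% coverage, 39-48% over 80-95%.

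**5. In-migrants in Direct MITT.** Arrival at 6-20 weeks gives up to 98 days each before arrival. Their number is not stated, so the total cannot be sized.

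**The case against.** Aim 2b shows the intent: start with the Overall population and stop at first OPV. Time before birth is impossible, so a competent programmer would probably query it. With randomised arms and balanced OPV1 timing, the ratio that defines effectiveness barely moves. In Direct MITT the pre-launch share of total time is small, and the SAP calls β2 from the first Cox model the best direct-effect estimate, with the Direct-population model as a second one. On a calendar time scale pre-launch risk sets contain no vaccinated infants, so that time does not influence the vaccine coefficient.

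Most of this stands and limits the reach. Three parts do not dispose of the point.
- Aim 2b does not say which Overall population it means. The secondary one starts at OPV1, so censoring at first OPV would leave no person-time. The primary one omits infants already past 6 weeks at launch, some of whom Indirect Population 2 admits.
- The second Cox model's time scale is not stated. The calendar-scale argument also needs risk sets formed within area, because the launches are five months apart, and it does not cover in-migrants' time before arrival.
- The study is unblinded and study staff attend EPI sessions to document consent to Rotarix, so equal OPV1 timing and uptake are not assured.

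Stronger readings are not supported. A reader might infer that all three faults affect both populations. They do not: pre-birth time arises only in Indirect Population 2, and pre-launch or pre-arrival time only in Direct MITT. A reader might infer that the effectiveness estimates are meaningless or that a false 20-27% indirect effect is to be expected. The latter needs an assumed 10% versus 6% non-uptake, which the SAP nowhere suggests. Nor did the vaccine arrive in government villages only on November 1: SAP 2.1 dates first use there to September 2008, so up to 61 of the 98 days may follow first use and the government-area Direct MITT figures lean high.

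**Conclusion.** Both rules are wrong as written, at secondary-aim severity.

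- **Indirect Population 2:** the rule contradicts Aim 2b and, applied literally, makes absolute rates unusable: about 7-9 fold too low with 10% never vaccinated, 8 to 148-fold with universal OPV1 at 56 to 3 days. The rate ratio is distorted only to the extent that OPV1 timing or uptake differs by arm.
- **Direct MITT:** the bias is modest and towards lower effectiveness if no cases are counted in the added time, about 4 to 6 percentage points from a true 50% at 90% coverage. The pre-launch part vanishes on a calendar time scale with risk sets formed within area.

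All sizes rest on uniform 6-week dates and the assumed delays, coverage and non-uptake. The primary analysis, which starts at 6 weeks or in-migration among infants reaching 6 weeks or arriving after launch, is not affected. Nor is Direct ATP, which starts at 26 weeks.

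**What to change.** In SAP 3.2, for both Indirect Population 2 and Direct MITT, start person-time at the latest of 6 weeks of age, the area launch date and the date of in-migration. Make Aim 2b in SAP 3.5 agree with the revised Indirect Population 2, naming the Overall population meant and saying whether infants aged 6-20 weeks on the launch date are included. State the time scale of the second direct-effect Cox model and whether risk sets are formed within area. This takes a few sentences, needs no new data and can be done before the analysis.
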